## Abstract

**Background:**

Support to strengthen the early parent-infant relationship is recommended to ensure the infant’s future health and development. Little is known about the universal approaches taken by health visitor to support this early relationship. The aim of this study is to investigate the effects of health visitors’ use of the Newborn Behavioral Observation (NBO) method among new parents.

**Methods:**

This is a cluster-randomised community-based study implemented in four Danish municipalities. Health visitors will conduct the trial, and the geographical districts they work in will constitute the clusters as units of randomisation. The participants will be approximately 2800 new families, randomised into an intervention or a comparison group according to their health visitor. The families are recruited at the first postpartum home visit. Parents in both groups receive care as usual: parents in the intervention group also receive the standardised NBO method in home visits performed from 3 weeks to 3 months postpartum. Data consist of self-reported parent questionnaires and video recordings of a selected group of vulnerable first-time mothers recorded 4 months postpartum. The self-reported data are obtained: at baseline 1 week postpartum and then at follow-up 3, 9 and 18 months postpartum. Data will be analysed using the intention-to-treat method and the analyses will include comparison of change in the primary variables across time supplemented by multiple regression analysis. The primary study outcomes are measured by the following factors: parental confidence, infants’ socio-emotional development and mother-infant relationship. Other measures include parental mood and stress, breastfeeding duration and utility of the health visitor services. Data collection among the health visitors in both groups will serve to monitor any change in practice regarding the work with early parent-infant interactions.

**Discussion:**

This protocol describes an evaluation of the NBO method used universally in health visiting practice. The intervention seeks to support early parenting by increasing parents’ understanding of their infants’ cues. The NBO is currently implemented in Denmark even though an evaluation of the NBO has yet to be made in a community setting in Denmark and internationally. The study may contribute to building an increasingly evidence-based practice for health visitors.

**Trial registration:**

ClinicalTrials.gov ID: NCT03070652. Registered February 22, 2017.

## Background

### Foundation of early parenting and parents at risk

The postnatal period is important for establishment of a healthy parent-infant relationship. The quality of this relationship is associated with the infant’s subsequent physical [1, 2] and psychosocial health [3–6] and cognitive development [7, 8].

In a general population of parents, a number of factors influencing the early parent-infant relationship have been identified [9–11]. First-time parents, in particular, tend to experience insecurity in responding to their infant’s cues [12], and fathers express more insecurity than mothers [13]. Insecurity is often present in the first weeks postpartum and among parents experiencing that their infant cries persistently or has sleep disturbances [14–17]. More than half of first-time mothers have reported that they experience difficulties and need of support in the early postpartum period [18, 19].

Preterm birth is another factor that may disturb the early parent-infant relationship. Parents of premature infants often experience anxiety, depression and decreased confidence in their own parenting capabilities. Combined with sorrow, stress, uncertainty and helplessness caused by the infant’s condition, this may impair parent-infant interaction [20, 21]. Worldwide, preterm birth is experienced by 11% of mothers; in developed countries by 6–8% [22].

Depressive symptoms in the postpartum period are also likely to impact on the quality of the parent-infant relationship [23–25]. Treatment of the parents’ depressive symptoms alone may be insufficient to protect children from poor long-term outcomes [23]. The estimated prevalence of parental postpartum depression is approximately 7–14% [25–27]. In previous research, one in five new Danish families showed signs of inadequate parenting due to low parenting confidence or parents had symptoms of depression [28].

Relationship disturbances are often more profound in families with cases of abuse, critical illness, domestic conflicts or mental illness, and may result in parent-infant-relationship disorder [9–11, 29].

### Effect of universal parenting support on the quality of the early parent-infant relationship remains unknown

The WHO and the Danish National Health Promoting Guidelines recommend early universal parental support [30, 31]. However, the effects of universal strategies for supporting early parenting remain unknown. The few reliable intervention studies available have focused mainly on parents at risk, such as mothers living in disadvantaged settings (32) or young less-educated mothers (33). These studies have shown that intervention brings significant long-term improvements in mortality for both mothers and infants [32] and a reduction in risky behaviour such as adolescence crime and medicine use among mothers [33].

In Denmark, health visitors provide early parenting support to approx. 95% of all Danish families, mainly through home visits [31]. The Danish Health Authority recommends that health visitors have a family-focused approach to healthy child development and that they focus on mental health and the establishment of an early parent-infant relationship. Previous studies have revealed that Danish health visitors believed that they are highly motivated for their jobs, have a high level of self-efficacy, are knowledgeable and have good observation skills as far as assessing the parent-infant relationship is concerned [34]. However, the health visitors do not use specific methods for supporting the establishment of the early parent-infant relation [31]. Moreover, little is known about the effect of universal programmes in Danish health visitor services. Only one trial has been conducted, showing a positive effect of home visiting on breastfeeding duration [35].

### Rationale of the newborn behavioral observation (NBO) method

The NBO is a standardised method designed to assist health visitors in their facilitation of the parent-infant relationship through shared systematic observation of the infant with their parents. The method is based on the comprehensive Neonatal Behavioral Assessment Scale (NBAS) [36] and on clinical experience with infants and their families. The method consists of 18 neuro-behavioural observations of the infant when sleeping, being awake or crying [37]. So far, the NBO method has been tested in the UK among high-risk families [38] and in China and the US among depressed mothers and in a hospital setting [39–42]. The previous studies found that NBO may increases the quality of care related to parent-infant social interaction and reduces depressive symptoms among mothers. Even though health visitors in their daily practice in the UK and Norway use the NBO, the method has yet to be examined in a universal preventive programme with a strong design and a large study population.

## Methods

### Aim and hypothesis

The aim of this study is to examine the short-term and long-term effects on child and family outcomes of the implementation of a universal NBO method provided by health visitors to a general population of parents in a community setting. We hypothesize that early parental support facilitated by the standardised NBO will increase parental sensitivity, confidence and mood, and that it will reduced parental stress. Moreover, we hypothesize that it will lead to improved infant socio-emotional behaviour and cognitive development and improve the early parent-infant relationship during the first 18 months of the infant’s life compared with families who are receiving standard care from health visitors.

### Design

This is a cluster-randomised, community-based study with two parallel arms implemented in four Danish municipalities. Health visitors will conduct the trial, and the geographical districts they work in will constitute the clusters. The design includes a pre-test at baseline 1–2 weeks after birth and post-tests at 3, 9 and 18 months after birth. Both the intervention and the comparison groups will receive standard care by health visitors. In addition hereto, the intervention group of mothers and fathers will receive support as the standardised NBO method will be applied at home visits from 3 weeks to 3 months after birth.

### Setting and recruitment

The trial is conducted in four Danish municipalities. Recruitment of the primary study population of new families was initiated on 1 January 2017 and is expected to continue until 31 January 2018. Data collection was initiated on 15 January 2017 and is expected to continue until 30 September 2019. At the first home visit after birth, health visitors recruit all new parents to participate in the trial. During this first visit, families receive oral and written information about the project and about data collection through self-reported questionnaires and video recordings. Mothers and fathers give their informed consent before participating. Parents are not informed about the group to which they belong.

### Participants

The study population consists of all new families in the four participating municipalities during the study period. The study population of parents is expected to represent the following subgroups: First-time parents (40%), premature births (7%), twin or triplet births (2%), postpartum depressed mothers and fathers (7–14%) and parents with a cultural background other than Danish depending on geographical area (7–20%) [43, 44].

All mothers and biological fathers or maternal partners who are visited by a health visitor 1–2 weeks after birth are eligible for the study. As this is a community-based universal intervention with no expected side effects in which we seek to measure the effect in a natural population of new parents, we have no exclusion criteria except for parents who are undergoing treatment elsewhere or are unable to manage their own legal affairs and are therefore not visited by a health visitor.

### Intervention

The NBO will be used among new parents in the intervention group at the health visitor examination of the newborn during the home visit when the infant is 3 weeks old, and in any subsequent home visits until the age of 3 months [37]. Through shared observation with the parents, the aim of the standardised NBO method is to enhance the parents’ sensitivity to their infant’s unique capacities, to create an early understanding of the individual infant’s strengths and needs, and to help the parents to interpret cues and interact with their newborn infant [37]. During the 18 neuro-behavioural observations focusing on the infant’s autonomic, motor, social interactive behaviour and state, the health visitor actively involves the parents in the systematic observations and shares the translation of the newborn infant’s expressions and cues with the parents [36]. As a result of the shared observation and assessment, the health visitor can give individual guidance to the parents on relationship-building, sleeping and crying patterns, etc.

The new parents in the comparison group will receive care as usual by health visitors. Examination of the newborn infant is already a part of health visitors’ practice during home visits after birth [31]. Health visiting practice in both groups follow the guidelines of the Danish Health Authority except for the difference in practice relating to the examination of the newborn infant [31].

### Health visitors, implementation and adherence

All authorised health visitors employed in the four participating municipalities who conduct home visits with new families are eligible and will be included in the study. In June 2016 before project start, participating health visitors were randomised to either the intervention or the comparison group according to their geographical districts.

In October 2016, all health visitors working in districts randomised to the intervention group received a 2-day NBO training course by certified NBO trainers followed by a training phase in which the health visitors practiced and completed a minimum of five NBO recordings before achieving their NBO certification in December 2016. A number of strategies ensured that the delivery of the NBO was in line with the standardised version. Firstly, each health visitor received a manual on the NBO method for the training course, and all health visitors joined a 1-h team Skype session twice during the training phase. Secondly, teams of health visitors from the intervention group participated in a 1-day workshop in March 2017 and also in a 2-h supervision session every third month during the intervention period. The general aim of these strategies was to motivate health visitors and facilitate the delivery of the NBO method by giving the health visitors an opportunity to ask questions and achieve feedback.

A linkage group was established at the beginning of the project consisting of the health visitor leaders from each of the four participating municipalities, the NBO trainer and the scientific investigators. The aim of this group is to coordinate and facilitate communication and involvement between the fields of practice and researchers. The group meets every 4 months during the planning and intervention period.

The delivery and thus the degree of implementation of the NBO intervention is continually registered by health visitors in the intervention group as they fill in a checklist during each home visit performed 3 weeks after birth to monitor which parts of the NBO was delivered during the visit. Additionally, data collection among the health visitors in both the intervention and comparison group aims at following any change in the health visitors’ knowledge, observation skills, intention and self-efficacy in their work with early parent-infant interactions.

### Data collection and study population

Data collection will continue among the participating parents until the child reaches 18 months of age. The data will consist of self-reported data and data coded from assessment of video interactions. Self-reported data from parents will be obtained at four time points via separate questionnaires to the mothers and fathers/partners at baseline 1–2 weeks postpartum and at follow-up at 3, 9 and 18 months postpartum. Questionnaires are collected via a web-based system with personal log in. Two reminders are sent by e-mail and SMS. Supplemental printed questionnaires are available for participants who do not have a computer or lack access to the internet. No monetary incentives are used to motivate participation. Lottery prizes representing a value of DKK 2000 will be drawn monthly from the pool of participants who complete the questionnaire.

In both the intervention group and the comparison group, a subgroup of 90 first-time mothers is selected consecutively among the responders for video recordings, which will be made about half way through the project period. The specified criteria for the subgroup are a low parenting confidence score, < 40 on the Karitane Parenting Confidence Scale (KPCS) [45], symptoms of depression (> 20 on the Major Depression Inventory (MDI) [46, 47]) or premature birth (< 37 gestational weeks). The aim of the video recording is to collect observational data to assess the quality of the mother-infant interaction. Data from the video recordings will be obtained at 4 months postpartum, adjusting for the age of premature infants [48]. The subgroup of mothers will be instructed to be with and interact with their infant as normally [48] while a 3-min video is recorded by a health visitor. Video coding will be performed by certified blinded CARE-Index raters; and to ensure inter-rater reliability, a random blinded sample will be coded and tested initially.

To minimise any bias introduced by data collection, data are collected in the same way and with the same timing in the intervention and comparison groups. Supplemental register data will be collected among non-participants and non-responders to facilitate assessment of the drop-out rate and its impact on the results.

### Outcome measures

The outcomes of the intervention are measured within three main domains: Parental status and development over time in parental confidence, mood, and stress; infant status and development over time in social, emotional and cognitive development; and, finally, interaction between parents and infant focusing on mother and infant interaction. The main outcomes are measured by validated scales and the Infant Care Index, a validated video-based observation system [48]. The main outcomes appear from Table 1.

**Table 1 Tab1:** Outcome variables for the primary study population and timing of data-collection

Separate self-reported questionnaire from the mother and father	2 weeks	3 months	9 months	18 months
Outcomes – parents				
Karitane Parenting Confidence Scale (KPCS)	x	x	x	
Major Depression Inventory (MDI)	x	x	x	x
Outcomes - infants				
Ages and Stages Questionnaire: Social-Emotional (ASQ:SE)	x	x	x	x
The Strengths and Difficulties Questionnaire (SDQ)				x
Ages and Stages Questionnaire (ASQ)			x	
Family relationship				
Mother and Baby Interaction Scale (MABISC)	x	x	x	x
Video observation mother-infant interaction, CARE-Index		x		

### Primary outcomes

*The Karitane Parenting Confidence Scale (KPCS)* by Črnčec et al. (2008) [45]. The KPCS consists of a 15-item questionnaire measuring parenting confidence in parents to infants aged from 0 to 12 months of age. The KPCS is rated on a four-point scale. The KPCS has not been validated in a Danish setting, but in an Australian context where it showed a good level of sensitivity (86%) and specificity (88%) [45]. The wording of the questions can be found in Črnčec et al. (2008) [45].

*The Ages and Stages Questionnaire: social-emotional (ASQ:SE)* by Squires et al. (1997) [49] consists of a questionnaire with 19–33 items measuring social-emotional problems and competencies in children regarding self-regulation, compliance, adaptive functioning, autonomy, affect, social communication and parent-children interaction in children aged from 1 month to 5 years. The ASQ:SE is rated by parents on a three-point scale; it includes a box where parents may report if the behaviour of their infant/child is a concern for them. The ASQ:SE has not been validated in a Danish context but internationally, showing a moderate to good sensitivity of 71–85% and an excellent specificity of 90–98% [49].The wording of the questions can be found in Squires et al. (1997).

*Video of mother-infant interaction coded by the Infant CARE-Index* by Crittenden (2006) consists of a video recording to assess the quality of mother-infant interaction (dyadic synchrony), the mother’s sensitivity and the infant’s cooperation in the interaction. The tree variables dyadic synchrony, maternal sensitivity and infant cooperation will be rated on a 0–14 point scale [48]. The 3-min videos will be collected 4 months after birth and coded by certified coders according to the Infant CARE-Index method [48]. To ensure the inter-rater reliability, the Cronbach’s alpha coefficient test of a consecutive blinded sample of the first ten collected video recordings will be analysed.

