### Statistical methods

Our data analyses will be in accordance with the CONSORT guidelines [58]. Intention to treat analysis will be used to detect the effect of the community-based intervention where participation may vary in the study population of parents. Following the intention to treat principle, mothers and fathers will remain in the group defined by the cluster randomisation. A baseline comparison of pre-defined background variables in the two groups will include unpaired t-tests and Fisher’s exact test. When testing the NBO with treatment as usual, the mean scores and any change in the primary variables across time in the intervention group from pre-test (at 2 weeks) to post-test at3, 9 and 18 months will be compared to mean scores and changes in the comparison group. Supplemental analyses will be performed to identify an intervention effect for subgroups and marginal groups of parents according to parity, preterm delivery and depression symptoms. Analyses will include multiple regression analysis to adjust for pre-randomisation variables such as parents’ age, marital status and educational background. Due to the small number of clusters, the analysis will include adjustment for within-cluster correlation. As we examine a relatively large number of outcomes, we will assess the robustness of our findings by applying methods suitable for multiple hypotheses testing. Finally, we will perform a drop-out analysis and examine the comparability of intervention and comparison group in the trial with respect to differences in received health visitor services.

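### ASQ:SE, a primary outcome, is scheduled at 1–2 weeks, below its stated 1-month age floor, and change from that score is a planned contrast; a baseline-adjusted comparison at each follow-up age would serve better

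*Protocol article*

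**What the plan says.** All places are in the protocol article.

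- **Age range.** Under Primary outcomes, ASQ:SE is said to measure several domains including "social communication and parent-children interaction in children aged from 1 month to 5 years".
- **Length.** The same paragraph says that it "consists of a questionnaire with 19–33 items". It does not say which form, or how many items, is used at any trial visit.
- **Schedule.** Table 1 (Outcome measures) marks ASQ:SE at 2 weeks and at 3, 9 and 18 months. Data collection and study population places the questionnaires "at baseline 1–2 weeks postpartum and at follow-up at 3, 9 and 18 months postpartum". The Design section agrees: "The design includes a pre-test at baseline 1–2 weeks after birth".
- **Analysis.** Statistical methods compares arms on mean scores and on change in the primary variables "from pre-test (at 2 weeks) to post-test at3, 9 and 18 months". The abstract puts change first and treats multiple regression as a supplement. The regression covariates listed are parental age, marital status and education, given as examples. The baseline value of the outcome is not named.
- **Contrast with KPCS.** KPCS, another primary outcome, is described for 0 to 12 months with a fixed 15 items, so its baseline is in range.

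**The concern.** Every ASQ:SE baseline is taken roughly two to three weeks below the age at which the protocol says the instrument starts, and no reason is given. That score then enters a planned effect measure for a primary outcome.

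There are two consequences. The first is interpretability: if the forms have different items at different ages, subtracting one total from another does not give movement on a single scale. The second is precision and balance: a pre-test that predicts later scores poorly adds its own variance to the difference and passes most of any chance baseline imbalance into it.

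ASQ:SE matters more than its place in the list suggests. In Table 1, KPCS stops at 9 months, and the CARE-Index video is a single recording at about 4 months with no pre-test. ASQ:SE is therefore the only primary outcome with 18-month data, while the stated aim covers the first 18 months.

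**Working it through.** **The plan's own figure.** No sample size or variance is given for ASQ:SE. The stated size concerns KPCS < 40 and reproduces: 25% versus 17%, two-sided 5%, 80% power gives 406 per arm, 812 in total; 812 × 1.15 = 934; 934 × (1 + 199 × 0.01) = 934 × 2.99 = 2793. It neither supports nor weakens this point.

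**Age and length.** The stated floor is 1 month and the baseline is 1–2 weeks, so every baseline score is out of range. If raw totals are used, the largest possible ratio of ranges between forms is 33/19 = 1.74. This is an upper bound: the 19–33 span runs to age 5 years, and the trial stops at 18 months.

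**Precision.** Let r be the within-arm correlation of the 2-week score with a later score, and k the baseline SD divided by the follow-up SD. Relative to follow-up alone (variance 1), at individual level and leaving clustering aside:

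- change: 1 + k² − 2kr, which is 2(1 − r) when k = 1
- baseline-adjusted (ANCOVA): 1 − r²

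Change is noisier than follow-up alone when r < k/2. ANCOVA is never worse than follow-up alone, since 1 − r² ≤ 1. It is never worse than change, since (1 + k² − 2kr) − (1 − r²) = (k − r)² ≥ 0.

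The documents give neither r nor k, so both are assumed. For k = 1, with power = Φ(2.80/√V − 1.96), where V is the relative variance and follow-up alone is set to 80%:

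| r | V, change | V, adjusted | Power, change | Power, adjusted |
|---|---|---|---|---|
| 0 | 2.0 | 1.00 | 51% | 80% |
| 0.1 | 1.8 | 0.99 | 55% | 80% |
| 0.3 | 1.4 | 0.91 | 66% | 84% |
| 0.5 | 1.0 | 0.75 | 80% | 90% |
| 0.7 | 0.6 | 0.51 | 95% | 98% |

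Against the adjusted comparison, change has 1.80/0.99 = 1.82 times the variance at r = 0.1 and 1.40/0.91 = 1.54 times at r = 0.3.

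**Sensitivity to unequal SDs.** The break-even r is 0.4 for k = 0.8 and 0.625 for k = 1.25. As extremes, let SD scale with form length:

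- shorter form at baseline, k = 19/33 = 0.58: change variance is 1.22 (r = 0.1) and 0.99 (r = 0.3) times follow-up alone
- longer form at baseline, k = 33/19 = 1.74: 1 + 3.02 − 0.35 = 3.67 (r = 0.1) and 1 + 3.02 − 1.04 = 2.97 (r = 0.3)

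**Imbalance.** With equal SDs and no treatment effect, a chance baseline difference d predicts a follow-up difference of rd. The change contrast is then rd − d = −(1 − r)d: a shift of 0.9d at r = 0.1 and 0.7d at r = 0.3, opposite in sign to d. Adjustment for baseline removes the predicted part rd from the follow-up contrast.

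**The case against.** The strongest reply is that the plan already compares mean scores, so much of what is wanted is there. It prescribes no simple subtraction: change over time could be estimated in a repeated-measures model. The covariate list is open-ended, and form-level scoring belongs to an analysis plan that is not shown. All of this stands, and it rules out several stronger readings.

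- A reader might infer that change is the only ASQ:SE effect measure. Statistical methods names mean scores as well.
- A reader might infer that the change score mainly adds noise, costing about 45% to 35% of the effective sample against an adjusted analysis (1 − 0.99/1.80 and 1 − 0.91/1.40). Those figures need r of 0.1 to 0.3 and equal SDs. Neither is documented, and above r = 0.5 change beats follow-up alone.
- A reader might take it as established that the visits use forms of different length. The article gives only the overall item range, so this is a probable inference.
- A reader might infer that baseline imbalance passes through in full. With equal SDs that needs r = 0. A recruitment difference that persists unchanged to follow-up would be removed by change scores and only partly by adjustment, but such persistence is hard to assume when the baseline score is out of range and perhaps on another scale.
- A reader might infer bias between arms. Data are collected in the same way and at the same times in both arms, so the age mismatch does not by itself bias the comparison.

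What the reply does not answer is the conflict between the stated floor and the schedule, or the use of that score in a planned primary contrast that the abstract puts first.

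**Conclusion.** The point holds in a limited form. The protocol contradicts itself on ASQ:SE: it states a 1-month floor and schedules the instrument at 1–2 weeks. Change from that pre-test is a planned contrast beside mean scores, and its meaning is doubtful if, as is likely, the forms differ between visits.

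The size of the precision loss is unknown. It is a loss against follow-up alone for r < 0.5 and a gain for r > 0.5 with equal SDs. A low r is plausible for an out-of-range score and a gap of up to 18 months, but it remains an assumption.

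The recommendation does not depend on it: the baseline-adjusted comparison is at least as precise as either alternative for any r and any SD ratio, in large samples and leaving clustering aside. This is an inexpensive improvement in interpretability and, probably, precision. It is not a demonstrated bias.

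**What to change.** For ASQ:SE:

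1. Drop change from 2 weeks as an effect measure.
2. Compare arms on the age-specific continuous score at 3, 9 and 18 months, with the 2-week score only as a covariate, and keep the planned adjustment for within-cluster correlation. Avoid replacing the score with a cut-off as the main analysis, since dichotomising usually loses precision.
3. Reconcile the 2-week administration with the stated 1-month floor: say which form is used at each visit and why the first is used at that age, and label the 2-week score as outside the stated range if it is.

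The cost is a change of wording in the statistical methods and the outcome description, ideally fixed before arms are compared. No new data, visits or participants are needed.

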### Sample size

Ongoing research shows that 25% of new mothers have a risk score < 40 on the KPCS [28]. Building the power calculation on an assumed loss to follow-up of 15%, a significance level of 5% and a power of 80%, calculations showed a need for 934 participating mothers to be able to identify a statistically significant difference decrease of 8% in reporting low confidence in understanding their infants. Taking an average of the relatively large cluster size into account (1 + (cluster size-1)*ICC), the desired number of participating mothers will be 934 X (1 + (200–1)*0.01) = 2793 mothers [56]. The included intraclass correlation coefficient (ICC) in the calculation is relatively low because the self-reported outcome is collected individually, and we do not expect mothers within clusters to be more alike than mothers across clusters. Moreover, earlier findings in similar research have shown a low cluster effect [35]. With the current birth rate in the participating municipalities, the number will require an inclusion and project period of approximately 12 months with follow-up at 3, 9 and 18 months.

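### Cronbach's alpha on the first ten videos cannot show a constant offset between CARE-Index raters, and the article describes the reliability sample in two incompatible ways

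*Protocol article*

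**What the plan says.** The Primary outcomes section of the protocol article lists the Infant CARE-Index among the primary outcomes and says that "dyadic synchrony, maternal sensitivity and infant cooperation will be rated on a 0–14 point scale". For inter-rater reliability it plans that the Cronbach's "alpha coefficient test of a consecutive blinded sample of the first ten collected video recordings will be analysed".

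The section on data collection and study population describes the same check differently: "to ensure inter-rater reliability, a random blinded sample will be coded and tested initially". On the coding itself it says: "Video coding will be performed by certified blinded CARE-Index raters". The number of raters, the share of videos coded twice and the way videos are assigned to raters are not given.

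On the number of videos it says: "In both the intervention group and the comparison group, a subgroup of 90 first-time mothers is selected consecutively among the responders for video recordings". This can be read as 90 in total or 90 per arm. The article names no other agreement statistic and describes no later reliability check.

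**The concern.** There are two separate problems.

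- **The sample.** The first ten consecutive videos are not a random sample. Both sections describe an early, blinded check, so timing and masking agree. The way the videos are picked does not.
- **The statistic.** Inter-rater reliability of a scored outcome should say how far the score depends on who did the scoring. Alpha answers a narrower question: how consistently the raters order and space the videos, once each rater's own mean level is removed. It also answers for the average of all raters, not for one.

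Two raters who differ by a fixed number of points on a 0–14 scale could therefore pass with a high alpha. If each then codes part of the videos alone, the offset goes into a primary outcome without having been noticed.

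**Working it through.** The article gives no reliability value, threshold or precision, so there is no figure to reproduce. The properties of the planned statistic were checked directly.

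**Inputs from the article:** three scales of 0–14; ten videos; more than one rater (plural); 90 videos in total or per arm. Ten videos are then 10/90 = 11% or 10/180 = 5.6% of the material.

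**Assumptions, not in the article:** two raters (three where stated), true between-video SD 2.5, error SD 1, offsets of 0 to 3 points, observed coefficient 0.80.

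**1. Effect of a constant offset d between two raters.**

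True variance is 2.5² = 6.25 and error variance is 1.

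- Alpha = 2 × 6.25 / (2 × 6.25 + 1) = 12.5/13.5 = 0.926. The offset does not enter the formula.
- Single-rater absolute-agreement ICC = 6.25 / (7.25 + d²/2).

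| Offset (points) | Alpha | Absolute-agreement ICC, single rater |
|---|---|---|
| 0 | 0.93 | 6.25/7.25 = 0.86 |
| 1 | 0.93 | 6.25/7.75 = 0.81 |
| 2 | 0.93 | 6.25/9.25 = 0.68 |
| 3 | 0.93 | 6.25/11.75 = 0.53 |

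A made-up set of ten videos scored by two raters, with all scores within 0–14, shows the same pattern. For shifts of 0, 1, 2, 3 and 4 points alpha is 0.975 throughout, while the absolute-agreement ICC is 0.955, 0.889, 0.737, 0.573 and 0.437.

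A difference in scale use is another matter. When one rater compressed the scale by half in the same example, alpha fell to 0.864. The blindness is therefore to constant offsets, not to every systematic difference.

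**2. Average of raters versus a single rater.**

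For k raters, the single-rater consistency ICC = alpha / (k − (k − 1) × alpha). At alpha 0.80:

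- k = 2: 0.80/(2 − 0.80) = 0.67
- k = 3: 0.80/(3 − 1.60) = 0.57

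**3. Precision with ten videos (F-based 95% intervals).**

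- Observed alpha 0.80, two raters. The 97.5% point of F with 9 and 9 degrees of freedom is 4.03. Lower limit 1 − 0.20 × 4.03 = 0.19; upper limit 1 − 0.20/4.03 = 0.95.
- Observed alpha 0.80, three raters: 0.41 to 0.95.
- Observed single-rater ICC 0.80, two raters. F = (1 + 0.80)/(1 − 0.80) = 9. One-way form, lower limit: 9/3.78 = 2.38, and (2.38 − 1)/(2.38 + 1) = 0.41. The upper limit is 0.95. The two-way consistency form gives 0.38 to 0.95.
- Thirty videos, observed alpha 0.80, two raters: 0.58 to 0.90.

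**4. What an undetected offset does to the outcome if each video is coded once.**

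- Videos split equally between the two raters in both arms: the outcome variance rises by d²/4, with no bias. For d = 2 the SD rises by √(8.25/7.25) − 1 = 7%; for d = 3 by √(9.5/7.25) − 1 = 14%.
- Unequal split: the bias in the arm difference is d times the difference between arms in the share coded by the second rater. As an illustration, shares of 60% and 40% with d = 2 give 2 × 0.20 = 0.4 points.
- Every video scored by all raters and averaged: the constant offset is the same in both arms and cancels.

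**The case against.** The strongest reply is that the harm depends on conditions the article does not state. Bias needs single coding, a material offset and unequal rater shares across the arms. Rater numbers, video allocation and the extent of double coding are details that an article commonly leaves to the full protocol. If all raters score every video and the scores are averaged, alpha describes the right quantity and an offset cancels. The raters are certified and blinded, which makes large offsets and coding divided by arm less likely. The 2- and 3-point offsets used above are chosen, not taken from the article. The check also concerns measurement quality in a selected video subgroup, not the treatment-effect analysis, and the sample size rests on a different outcome, the KPCS.

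Most of this stands, and it limits the consequence. It does not remove the point, because the article itself fixes both the statistic and the sample: it names one that cannot show offsets and describes the other in two ways. Blinding limits differential scoring but does not balance raters across arms.

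A reader might infer more than the text supports:

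- **That alpha misses every systematic disagreement.** It does respond to differences in scale use, as the compressed-scale example shows.
- **That the primary comparison is biased.** Nothing in the article says that raters are unevenly spread over the arms.
- **That the data collection section promises a sample spread over the coding period or drawn from both arms.** It says that the check is done at the start and says nothing about arms. Lack of a later drift check contradicts neither section.
- **That the first ten videos come from few districts or mainly one arm, or that a baseline video would have solved the problem.** The first is a guess. A baseline would remove an offset only if the same rater scored both recordings.

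**Conclusion.** The point holds in a limited form. The two descriptions of the reliability sample contradict each other in current text and must be reconciled. Cronbach's alpha cannot reveal a constant severity difference between raters. If videos are single-coded, it also overstates the reliability of the score analysed (0.80 for the average corresponds to 0.67 for one of two raters). Ten videos cannot separate poor from excellent reliability: an ICC of 0.80 has a 95% interval of about 0.41 to 0.95 with two raters.

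The likely cost to the trial is noise, of the order of a 7% to 14% larger SD for offsets of 2 to 3 points under the stated assumptions. Bias arises only with unequal rater shares between arms. The mathematical property of alpha needs no assumption; the sizes rest on the assumed SDs, rater numbers, offsets and coding scheme. This is a correction worth making to the quality check on a primary outcome, not a threat to the trial's validity.

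**What to change.** 1. State one sampling rule in both sections: a random blinded sample, as the data collection section already says. Give its size, preferably more than ten videos.
2. Replace alpha, or supplement it, with a two-way absolute-agreement ICC and 95% confidence interval for each of dyadic synchrony, maternal sensitivity and infant cooperation. Use the single-rater form if videos are coded once and the average form if raters' scores are averaged, and say which applies.
3. Report the mean difference between raters on each scale, in points.

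Balancing raters across the arms would also remove the route by which an offset could become bias. That is good practice beyond the correction itself.

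The cost is wording. If more than ten videos are double-coded, it adds modest coding time by the existing raters. No further recordings are needed.
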